## Abstract

**Background:** Brain plasticity is an intrinsic property of the nervous system, which is modified during its lifetime. This is one mechanism of recuperation after injuries with an important role in rehabilitation. Evidence suggests that injuries in the nervous system disturb the stability between inhibition and excitability essential for the recuperation process of neuroplasticity. However, the mechanisms involved in this balance are not completely understood and, besides the advancement in the field, the knowledge has had a low impact on the rehabilitation practice. Therefore, the understanding of the relationship between biomarkers and functional disability may help to optimize and individualize treatments and build consistent studies in the future.

**Methods:** This cohort study, the deficit of inhibition as a marker of neuroplasticity study, will follow four groups (stroke, spinal cord injury, limb amputation, and osteoarthritis) to understand the neuroplasticity mechanisms involved in motor rehabilitation. We will recruit 500 subjects (including 100 age- and sex-matched controls). A battery of neurophysiological assessments, transcranial magnetic stimulation, electroencephalography, functional near-infrared spectroscopy, and magnetic resonance imaging, is going to be used to assess plasticity on the motor cortex before and after rehabilitation. One of the main hypotheses in this cohort is that the level of intracortical inhibition is related to functional deficits. We expect to develop a better understanding of the neuroplasticity mechanisms involved in the rehabilitation, and we expect to build neurophysiological “transdiagnostic” biomarkers, especially the markers of inhibition, which will have great relevance in the scientific and therapeutic improvement in rehabilitation. The relationship between neurophysiological and clinical outcomes will be analyzed using linear and logistic regression models.

**Discussion:** By evaluating the reliability of electroencephalography, functional near-infrared spectroscopy, transcranial magnetic stimulation, and magnetic resonance imaging measures as possible biomarkers for neurologic rehabilitation in different neurologic disorders, this study will aid in the understanding of brain plasticity mechanisms in rehabilitation, allowing more effective approaches and screening methods to take place.

## Introduction

The brain is designed and molded by environmental changes, pressures, and experiences (1). In this context, brain plasticity is understood as an intrinsic and permanent property of the nervous system, which is in constant modification during the human lifetime (1–3). This property allows the partial or total recovery after injuries to the human nervous system, and it involves recovery or compensation and motor adaptation with assistive technologies (3). Throughout life, the human brain is flexible, adapts quickly to environmental changes, and simultaneously, preserves a relatively stable balance between the long-term potentiation and the long-term depression or excitability and inhibition (4, 5). However, evidence suggests that injuries in the nervous system unbalance neural stability (6). For example, recently, evidence has shown that a deficit in neuronal inhibition is detected in patients with a disability regardless of etiology (7–9), and this lack of inhibition is associated with more disability (10). The understanding of brain plasticity has advanced; however, this knowledge has had a low impact on the rehabilitation practice (1). Furthermore, the mechanisms involved in the excitability and the inhibition balance and in brain plasticity regulation are not completely understood, as the biomarkers would be able to measure these processes. Also, there is a lack of studies designed to understand the mechanisms of brain plasticity in the context of rehabilitation, and there are no reliable biomarkers in the rehabilitation field nowadays. Therefore, this study's objective is to identify, through transcranial magnetic stimulation (TMS), electroencephalography (EEG), and functional near-infrared spectroscopy (fNIRS), biomarkers that represent the imbalance in the cerebral activity and its impact on rehabilitation, optimizing, and individualizing treatments and resources. Consequently, this project looks to understand the relationship between the biomarkers and the functional impairment related to the disability, regardless of the etiology. For that reason, we designed this cohort study with four conditions in neurorehabilitation: stroke, spinal cord injury, limb amputation, and knee osteoarthritis (OA). We selected these four conditions to represent conditions with different levels of neural lesions (i.e., stroke for central lesions, spinal cord injury to central lesion but in spinal cord, phantom limb pain for peripheral lesion but more proximal, and OA for peripheral lesion and more distal). Subjects included in this cohort are tested in the baseline with comprehensive neurophysiological assessments to assess different measures of neuroplasticity and especially inhibitory activity of the motor cortex and also a comprehensive clinical assessment to correlate to functional deficits.

## Methods and Analysis

### Participants and Study Design

This is a prospective cohort study made up of four groups with a specific diagnosis (stroke, spinal cord injury, knee OA, or lower limb amputation) and a group of healthy volunteers.

Patients admitted to the conventional rehabilitation program of the Instituto de Medicina Física e Reabilitação (IMREA) will be invited to participate in the study and included after signing the informed consent form previously approved by the Hospital das Clínicas da Faculdade de Medicina da Universidade de São Paulo Ethics Committee for Research Protocol Analysis CAAE: 86832518.7.0000.0068. For this study, 400 patients will be recruited, 100 patients with a stroke diagnosis, 100 with knee OA, 100 with spinal cord injury, and 100 amputee patients. The control group will be made up of 100 healthy subjects paired by sex and age.

Patients who agree to participate in the study will undergo a series of assessments at two time points: before and after the IMREA rehabilitation program. An individualized approach characterizes this program, considering the injury's etiology, the type of disabilities the patient has, general clinical conditions, likely prognosis, and the patient's socioeconomic factors. The control group will only perform neurophysiological (EEG, fNIRS, and TMS) and functional assessments once.

It is important to note that all patients involved in the research will receive the same type of treatment as patients who are not participating in the research.

### Sample Size

The sample size of 100 patients for each type of injury was determined, given this is an observational study (prospective cohort) and, thus, the primary analysis being a linear regression. Therefore, 100 participants in each group will allow for the modeling of 10 covariates, which will yield an effect size of ~0.3, which we believe is enough, mainly due to the use of neurophysiological variables and our knowledge of previous studies. Our group recently performed two studies with multivariate analyses, one with 35 and another with 55 patients, to assess neurophysiological markers (EEG and TMS), which allowed us to identify the role of these markers in the rehabilitation of conditions such as stroke.

Thus, using a larger sample (100 subjects), compared with our previous studies, associated with a larger detailing of clinical and neurophysiological information, will aid in the better comprehension of cerebral plasticity. We also believe this sample size will yield similar results for patients with knee OA, spinal cord injury, and amputation. Furthermore, it will allow for the identification of transdiagnostic markers, not aiming to compare the different injury groups but to determine the neurophysiological alterations they have in common.

### Inclusion Criteria

Participants of both sexes will be included in the study if they are older than 18 years, have confirmed clinical stability verified by medical evaluation, have signed the informed consent form, and if they fulfill the eligibility criteria for the IMREA rehabilitation program. To be included in the specific injury groups, patients will have to have a clinical, and radiological [magnetic resonance imaging (MRI) or computerized tomography; or bilateral knee radiography] diagnosis of stroke (confirmed by computed tomography scan and/or MRI), spinal cord injury, or knee OA (clinically confirmed) or a clinical diagnosis of bilateral or unilateral lower limb amputation.

### Exclusion Criteria

Subjects will be excluded if they are pregnant, have active OA with clinical manifestations in joints other than the knee, or if they have any other clinical or social conditions that interfere with the patient's participation in the rehabilitation treatment.

### Clinical and Functional Assessments

At the beginning of the study, on the participant's first visit, a trained physician will take the patient's history, perform a physical examination, and review the eligibility criteria for that patient. The obtained information from the patient's history such as age, sex, height, weight, ethnicity, education level, medications in current use, comorbidities, and the specific characteristics of each injury will be used as covariates in the final linear regression model.

Several instruments that allow the global assessment of participants, general or specific to each condition, were selected (Table 1 and Appendix 1). Some scales, such as cognitive, sleep, and mood scales, will be used to characterize the study's sample, as well as for the management of confounding variables on the multivariate statistical model.

**Table 1 T1:** Assessment instruments used for each study group.

**Category**	**Instrument**	**Amp**.	**Stroke**	**OA**	**SCI**	**CG^*^**
Independence	Functional Independence Measure (FIM) (11)	X	X	X	X	X
Independence (Specific to SCI)	Spinal Cord Injury Independence Measure (SCIM III) (12)				X	
Cognition	Montreal Cognitive Assessment (MOCA) (13)	X	X	X	X	X
Cognition (speach)	Semantic verbal fluency test (14)		X			
Pain	Conditioned Pain Modulation (CPM) (15)	X	X	X	X	X
Pain	Pressure Pain Threshold (PPT) (16)	X	X	X	X	X
Pain/Sensitivity	Monofilament Sensitivity Test (17)	X	X	X	X	X
Pain/Sensitivity	Tuning Fork Vibration Sensitivity Test (18)	X	X	X	X	X
Pain	Pain Catastrophizing Scale (19, 20)	X	X	X	X	
Pain	McGill Pain Questionnaire (Brazilian Version) (21)	X	X	X	X	
Pain	Visual Analogue Scale (VAS) for Pain (22)	X	X	X	X	
Lower Limb Motor Function	6-min and 10 meters gait test (23)	X	X	X	X	X
Lower Limb Motor Function	Timed Up and Go (TUG) (24)	X	X	X	X	X
Lower Limb Motor Function	Lower Limb Isokinetic Dynamometer (25)	X	X	X	X	X
Lower Limb Motor Function	Walk Index for Spinal Cord Injury (WISCI-II) (26)				X	
Upper Limb Motor Function	Fugl–Meyer Assessment (FMA) (27)		X		X	
Upper Limb Motor Function	Hand Grip and Pinching (28–30)		X		X	X
Upper Limb Motor Function	Purdue Pegboard Test (PPBT) (31)		X		X	X
Upper Limb Motor Function	Robot-Measured Kinematic Variables (32)		X		X	X
Upper Limb Motor Function	Finger Tapping (FT) (33)		X		X	X
Upper and Lower Limb Motor Function	Medical Research Council Scale (MRC) (34)		X	X	X	
Balance	Force platform (35)	X	X	X	X	X
Balance	Berg Balance Scale (36)	X	X	X	X	
Spasticity	Modified Ashworth (37)		X		X	
Sleep	Epworth sleepiness scale (38)	X	X	X	X	X
Mood	Hamilton Depression Rating Scale (HAM-D) (39)	X	X	X	X	X
Mood	Hospital Anxiety and Depression Scale (HADS) (40)	X	X	X	X	X
Pain, rigidity, and daily activities	Western Ontario and McMaster Universities Osteoarthritis Index (WOMAC) (41)			X		
Lower limb	Amputee Mobility Predictor (AMP) (42)	X				
Amputation	Quebec User Evaluation of Satisfaction with Assistive Technology (QUEST 2.0) (43)	X				
Stroke	National Institutes of Health Stroke Scale (NIHSS) (44)		X			
SCI	American Spinal Injury Association Impairment Scale (ASIA) (45)				X	
OA	Kellgren-Lawrence Radiographic Classification of OA (46)			X		
OA	Ultrasound Assessment (US)			X		
Quality of life	Stroke Impact Scale (SIS) (47)		X			
Quality of life	Medical Outcomes Short-Form Health Survey (SF-36) (48)	X	X	X	X	X
Polymorphisms	Genetic Polymorphism Analysis (49)	X	X	X	X	X

* *Control group*.

The same evaluator will preferably carry out assessments. Evaluators will be trained to standardize questionnaire applications to reduce assessment subjectivity.

A detailed explanation of all the scales and tests used in this study under Supplementary Material.

### Neurophysiological Assessment Methods

#### Transcranial Magnetic Stimulation

The Magstim Rapid® stimulator (The Magstim Company Limited, United Kingdom) and a 70-mm coil in figure-of-eight will be used, positioned tangentially to the skull and at an angle of 45° in relation to the sagittal line will be used. The muscular response to the stimulus applied to the motor cortex will be recorded using surface electromyography with Ag/AgCl electrodes positioned on the target muscle and the grounding electrode positioned on the wrist. We will follow the methods established in the literature for physiological and clinical studies (50).

Bilateral upper limb assessment (first dorsal interosseous muscle of the hand) will be performed. The motor area corresponding to the first dorsal interosseous is the most used motor cortical area in cortical excitability studies in addition to presenting a greater accuracy of the method due to the local anatomy and penetration of the TMS pulse. To locate the cortical area of the hand, it will initially be identified from the vertex (intersection between the nasion–inion lines and zygomatic arches). Then, for the identification of the probable hot spot, a mark will be made 5 cm from the vertex toward the ear tragus in the coronal plane. The hot spot will be defined as the location as the lowest resting motor threshold and with the greatest amplitude of the motor evoked potential in the target muscle for a given intensity of the upper threshold stimulus.

The resting motor threshold (rMT) will be defined as the minimum intensity necessary for a single TMS pulse on the hot spot to generate an evoked motor potential (EMP), with at least 50 μV peak-to-peak amplitude, in 50% of attempts. rMT will be used as an indirect measure of cortical excitability. In addition, the following measures will be used: resting EMP, in which motor 10 EMPs will be recorded, with an interval of ~7 s between stimuli; silent period (SP), which represents the temporary suppression of electromyographic activity during a sustained EMP voluntary contraction; intercortical inhibition (SICI), which will be assessed by interstimulus intervals of 2 ms. The conditioned stimulus intensity (CS) will be set at 80% rMT and the test stimulus intensity (TS) adjusted to induce MEPs of ~1 mV peak-to-peak amplitude. Also, finally, intracortical facilitation (ICF) will also be measured by 10-ms interim stimulus intervals, and CS intensity will be the same as it was for the SICI evaluation.

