### Statistical Analysis

For this analysis, we will use the multivariate regression model in which motor improvement will be the dependent variable and changes in inhibitory activity (resulting from neurophysiological assessments performed before and after treatment) will be the independent variables.

To control the impact of different conditions on the multivariate model, we will create a “dummy variable” for each disease etiology. Moreover, demographic characteristics (age, education, sex, and ethnicity) and clinically relevant characteristics (duration of illness, comorbidities, and the use of medications) will be tested, as well as specific aspects for each disease, such as the stroke side, the level of spinal cord injury, the degree of bone deformity of knee OA, and the level of lower limb amputation. The neurophysiological biomarkers described earlier will be tested in the same model.

Although this study's aim is not to test interventions but to identify changes in biomarkers related to functional improvement (regardless of the therapy performed), the different therapies performed by patients will be quantified, including information such as the number of sessions, frequency, duration, among others, which can be used in future analyses.

For secondary analyzes, functional improvement can be assessed by the several, general and specific, scales used depending on the evaluated disease. In this situation, we will use the calculation of the functional modification's effect size and not the absolute values of the scale for the analysis in the multivariate model.

Also, the motor function of the upper limb will only be assessed for patients with stroke and spinal cord injury, the main scale used being the Fugl–Meyer Assessment. In this case, an analysis similar to the one described earlier will be performed but only including these two populations.

Some of the scales, such as those for mood, pain, cognition, and sleep, will be used to characterize the sample, in addition to possibly being used to control confounders in the multivariate model. Besides, mood, pain, and cognitive disorder are commonly present in these populations, so we will perform an exploratory analysis using a similar statistic method but with scales related to these aspects as dependent variables.

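### SICI, ICF and the silent period cannot be measured in the most impaired hands, so testing them as change scores in one model loses stroke and spinal cord injury patients in a severity-dependent way

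*Protocol article*

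**What the plan says.** **Where TMS is measured.** Under Transcranial Magnetic Stimulation in the protocol article: "Bilateral upper limb assessment (first dorsal interosseous muscle of the hand) will be performed". No other target muscle is named for any group.

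**What each marker requires** (same section):
- rMT: a response of at least 50 μV "peak-to-peak amplitude, in 50% of attempts".
- SICI and ICF, conditioning pulse: "The conditioned stimulus intensity (CS) will be set at 80% rMT", so an rMT must exist first.
- SICI and ICF, test pulse: "the test stimulus intensity (TS) adjusted to induce MEPs of ~1 mV peak-to-peak amplitude".
- Silent period: a quantity "which represents the temporary suppression of electromyographic activity during a sustained EMP voluntary contraction".

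**Who is eligible.** Inclusion Criteria and Exclusion Criteria, as shown, ask for adult age, clinical stability, a confirmed diagnosis and eligibility for the rehabilitation program. They ask for no residual hand movement and no obtainable evoked response. They do not restrict the level of spinal cord injury, which Statistical Analysis lists as a characteristic to be tested in the model.

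**How the markers are used.** The Abstract gives as a main hypothesis that "the level of intracortical inhibition is related to functional deficits". Statistical Analysis regresses motor improvement on before-after changes in inhibitory activity and adds: "The neurophysiological biomarkers described earlier will be tested in the same model".

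**The concern.** Whether SICI, ICF or the silent period can be measured depends on how much corticospinal function the hand retains, and that is close to the deficit under study. The Discussion itself describes motor severity as strongly associated with rMT. Hands without a measurable response should therefore be concentrated at the severe end.

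Two things follow. The association between inhibition and deficit would be estimated in a sample restricted towards milder patients, which weakens the association as well as reducing the number analysed. And a patient with no response at baseline who regains one during rehabilitation has no before-after change in these markers, although that patient is among the most informative for the substitute type of biomarker described in the Discussion.

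The Discussion mentions severity only as a cause of unequal dropout that may unbalance group sizes. It does not treat severity as a reason why the marker itself may not exist.

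**Working it through.** **Step 1. Definitions against eligibility.**

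| Marker | Needs from the hand | Required for entry, as shown? |
|---|---|---|
| rMT | 50 μV at rest in half of attempts | No |
| SICI, ICF | an rMT and a test response of about 1 mV | No |
| Silent period | sustained voluntary contraction | No |

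A hand with no response yields none of these. A hand with a weak response may yield rMT but not SICI or ICF. A change score needs a value at both visits, so one unobtainable visit is enough to lose it.

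**Step 2. The plan's own figure.** Sample Size gives 100 per group, 10 covariates and an effect size of about 0.3. The metric, alpha and power are not stated, so the figure cannot be reproduced uniquely. Reading 0.3 as a partial correlation for one coefficient, with two-sided alpha 0.05 (assumed), the noncentrality is n·r²/(1−r²) = 100 × 0.09/0.91 = 9.89 on 1 and 89 degrees of freedom, which gives power 87.5%. Reading it as Cohen's f = 0.3 gives 84%. The figure is plausible for 100 complete patients, with no allowance for unobtainable markers.

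**Step 3. Effect of severity-dependent loss.** The documents give no rate, so the share lost, q, is assumed to be 10, 20 or 30% of one injury group. Let inhibition level and deficit severity be bivariate normal with correlation 0.30. Let unobtainability be a latent normal variable that correlates ρ with severity and is otherwise unrelated to inhibition. The top q of that variable is lost.

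- c = Φ⁻¹(1−q), λ = φ(c)/(1−q), V = 1 − cλ − λ²
- A = 1 − (1−V)ρ²
- r observed = 0.30·√A / √(1 − 0.09(1−A))

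For q = 10%: c = 1.2816, λ = 0.1950, V = 1 − 0.2499 − 0.0380 = 0.7121.
- ρ = 1: A = 0.7121, r = 0.30 × 0.8438/√(1 − 0.09 × 0.2879) = 0.2532/0.9870 = 0.26.
- ρ = 0.7: A = 1 − 0.2879 × 0.49 = 0.8589, r = 0.2780/0.9936 = 0.28.

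For q = 20% and 30%, V = 0.5830 and 0.4928. Power is computed as in Step 2, with n = 90, 80 or 70 and 10 predictors.

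| Lost | n | r at ρ = 1 | r at ρ = 0.7 | r at ρ = 0.5 | Power at ρ = 1 | Power at ρ = 0.7 | Power, random loss |
|---|---|---|---|---|---|---|---|
| 10% | 90 | 0.26 | 0.28 | 0.29 | 70% | 78% | 83.8% |
| 20% | 80 | 0.23 | 0.27 | 0.29 | 56% | 70% | 79.2% |
| 30% | 70 | 0.22 | 0.26 | 0.28 | 44% | 61% | 73.5% |

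The ρ = 1 column is the worst case: the patients lost are exactly the most severe.

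**Step 4. The improvement model.** Step 3 concerns level against deficit. The stated regression relates improvement to change. If unobtainability correlates −0.3 with improvement (assumed), ρ² = 0.09 and A = 0.974, 0.962 and 0.954, which gives r between 0.29 and 0.30 for all three shares. Attenuation is small there; what remains is the smaller sample and the loss of patients who regain a response.

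**The case against.** **Patients with no value at all.** A reader might infer that severely affected patients have no TMS data. The article does not support that. TMS is bilateral, so in unilateral stroke the less affected hemisphere can still be measured. Knee osteoarthritis and lower-limb amputation, half of the 400 patients, carry no stated hand deficit. Resting evoked-potential amplitude is also recorded, and an absent response might be entered there as near zero, although the stimulus intensity is not stated. The gap in SICI, ICF and the silent period on the affected side remains, and the less affected side does not measure the lesioned cortex. The article does not say which side enters the model.

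**Certain deletion.** A reader might also infer that the plan prescribes dropping these patients. It states no complete-case rule, and missing-data handling may sit in a document not shown. Testing in the same model need not mean entering every marker at once. Loss is therefore what an ordinary regression fit would do, not a stated rule. But no missing-data rule can make SICI exist where there is no response, and entering markers one at a time would spare the EEG data while leaving SICI restricted to measurable hands.

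**Intact EEG and fNIRS data.** This holds only in part. Both include executed hand movements, which a plegic hand cannot perform. Rest and imagery data, and movement observation in the EEG, remain.

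**Size.** The largest attenuation requires unobtainability to be identical to severity, and it concerns level against deficit. Both limits are accepted and shown above. Program eligibility criteria that are not shown may also exclude some of these patients.

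**Conclusion.** The point holds in limited form. By the article's own definitions, SICI, ICF and the silent period, and often rMT, are unobtainable in the most impaired hands. The criteria as shown admit such patients, and a single model built on change scores would, under ordinary fitting, lose them in a way that depends on the deficit under study.

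The number affected is unknown. For an assumed loss of 10, 20 or 30% of one injury group, a true level-deficit correlation of 0.30 would be observed as 0.26, 0.23 or 0.22 at worst, and as about 0.28, 0.27 or 0.26 if unobtainability correlates 0.7 with severity. These figures rest on bivariate normality and on the assumed shares and correlations. For improvement against change, attenuation may be negligible. The change is worth making because it is cheap and because response status is hard to reconstruct later: an absent response that was not recorded as such may look like a test that was not done.

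**What to change.** In Transcranial Magnetic Stimulation and Statistical Analysis:

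1. Record response status (present, or absent at maximum stimulator output) for each hemisphere and visit. Enter it as a TMS marker for stroke and spinal cord injury, including change from absent to present.
2. Fit the EEG and fNIRS markers in a model that does not require SICI, ICF or the silent period. Note that EEG and fNIRS data from executed hand movements will also be limited for a plegic hand.
3. State that SICI, ICF and silent-period results apply to hemispheres with a measurable hand response.

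**Cost.** One field per hemisphere and visit on the case report form, plus analysis wording. No new procedure is needed, because the stimulation session already shows whether a response is obtained. The price is one extra, coarser marker and separate TMS and EEG/fNIRS models in place of one.
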